**Long-term outcomes**	
Renal function decline	Diagnosed with chronic renal failure and could not be attributed to other known causes
Type I endoleak	Endoleak due to inadequate proximal or distal seal of the stent graft
Type II endoleak	Endoleak originating from collateral vessels
Type III endoleak	Endoleak resulting from stent graft component separation or fabric tear
Stent migration	Migration from original position for more than 5 mm
Aneurysm related death	All deaths from secondary aneurysm rupture after repair, death within 30 days of any reintervention attributable to the aneurysm or death from other aneurysm-related causes (including graft infection or fistula)

MALEs, major adverse limb-graft events; EVAR, endovascular aneurysm repair; MACEs, major adverse cardiac events.

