### Outcomes of interest

The primary outcome is 3-year freedom from MALEs, which involves type IB/III endoleak and limb occlusion. Type IB endoleak is defined as persistent direct flow in the aneurysm sac due to inadequate distal seal of the stent graft. Type III endoleak is defined as persistent direct flow resulting from stent graft component separation or fabric tear. Limb occlusion is defined as a total occlusion occurring in limb grafts, regardless of symptoms, or an invasively treated stenosis resulting from thrombus formation (> 50% lumen reduction).

The secondary outcomes involve 3-year freedom from type IA endoleak and 3-year freedom from aortic reintervention. Type IA endoleak is defined as persistent direct flow in the aneurysm sac due to inadequate proximal seal of the stent graft. Aortic reintervention refers to any secondary surgical procedure related to the index EVAR.

Other outcomes consist of three aspects: intraoperative technical outcomes (operation time, radiation exposure time, dosage of contrast medium and technical success rate); short-term postoperative outcomes (length of stay in intensive care unit or vascular ward, acute kidney injury, 30-day overall morbidity, 30-day major adverse cardiac events, 30-day all-cause mortality); long-term outcomes (renal function decline, occurrence of type I/II/III endoleak or stent migration, freedom from major adverse cardiac events, aneurysm related death, overall survival).

Detailed information for outcomes is listed in Table 2.

**TABLE 2 T2:** Detailed information for outcomes.

Outcomes	Definition

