**Short-term postoperative outcomes**	
Acute kidney injury	Serum creatinine elevates by 0.3 mg/dL or 50% compared with baseline within 48 h; or urine less than 0.5 mL/kg/h for more than 6 h
30-day morbidity	The existence of any adverse event within 30 days, consisting of infection, pseudoaneurysm, deep venous thrombosis, hypoalbuminemia, hemorrhage, embolism, stroke, buttock ischemia and systematic complications such as pulmonary, cardiac, cerebral and bowel events
30-day MACEs	Diagnosed with myocardial infarction, chronic cardiac failure, or receive repeat revascularization or died within 30 days

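### Table 2 names 30-day death after a reintervention, but not after the index EVAR, as aneurysm-related, and words two 30-day MACE components too loosely

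*Protocol article*

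**What the plan says.** In the protocol article, Table 2 (Long-term outcomes) gives aneurysm-related death three parts. The first two are "All deaths from secondary aneurysm rupture after repair, death within 30 days of any reintervention attributable to the aneurysm". The third is "death from other aneurysm-related causes (including graft infection or fistula", an open clause with two examples. Under Outcomes of interest, the article explains what a reintervention is: "Aortic reintervention refers to any secondary surgical procedure related to the index EVAR".

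Table 2 (Short-term postoperative outcomes) defines 30-day MACEs as "Diagnosed with myocardial infarction, chronic cardiac failure, or receive repeat revascularization or died within 30 days". The table footnote expands the abbreviation as "MACEs, major adverse cardiac events".

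Outcomes of interest lists among the short-term outcomes "30-day overall morbidity, 30-day major adverse cardiac events, 30-day all-cause mortality" and among the long-term ones "freedom from major adverse cardiac events, aneurysm related death, overall survival". All of these belong to the third tier, headed as other outcomes, below the primary outcome (3-year freedom from MALEs) and the two secondary outcomes.

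**The concern.** The crossed or standard configuration is created during the index EVAR. If it causes early deaths, they occur in the weeks after that operation. The definition of disease-specific death gives a fixed 30-day rule for later procedures and none for this one. Classification of early deaths then depends on how each assessor reads the open clause. The surgeons know the configuration; the article states blinding only for the statisticians who analyse the data.

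The MACE row raises a related problem of specificity. Chronic cardiac failure is a condition that a patient may bring to the operation, and the row does not ask that it be new or worse. Repeat revascularization is not tied to the coronary arteries, in a trial whose primary outcome counts limb occlusion, including stenosis treated invasively. An early limb procedure could therefore be scored as a cardiac event.

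**Working it through.** The document gives no figure to reproduce, so the check compares the definitions.

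**Step 1. Can a death soon after the index EVAR meet a named part of aneurysm-related death?**
- Reintervention clause: no. A reintervention is a secondary procedure, so the index EVAR is not one.
- Rupture clause: only for rupture that is secondary and follows repair. Table 1 does not list ruptured presentation as an exclusion, and a death from the presenting rupture is not of that kind.
- Open clause: possibly, if an assessor decides so. The word introducing its examples shows that they are not exhaustive.

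**Step 2. Apply the wording to one death**, for example from bowel ischaemia on day 10.

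| Outcome | Day 10 after an aneurysm-attributable reintervention | Day 10 after the index EVAR |
|---|---|---|
| Aneurysm-related death | Yes, by rule | Only if placed in the open clause |
| 30-day MACE | Only if also within 30 days of the index EVAR | Yes, since any death counts |
| 30-day all-cause mortality | Only if also within 30 days of the index EVAR | Yes |
| Overall survival | Event | Event |

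The first row shows the inconsistency: the same death is classified differently according to which procedure it followed. The last two rows show that the death is still counted.

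**Step 3. Compare the MACE components with neighbouring rows.** Table 2 sets conditions of this kind elsewhere. Acute kidney injury is judged against the baseline creatinine, and renal function decline must not have another known cause. The cardiac failure component has no such condition, and revascularization has no vascular territory.

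**Step 4. How many deaths could be affected?** The document gives no 30-day mortality. Assume 1% to 3%:
- Whole trial: 275 × 0.01 = 2.75 and 275 × 0.03 = 8.25, so about 3 to 8 deaths.
- Crossed-limb group: 73 × 0.01 = 0.73 and 73 × 0.03 = 2.19, so about 1 to 2.
- Standard-limb group: 202 × 0.01 = 2.02 and 202 × 0.03 = 6.06, so about 2 to 6.

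One reclassified death moves the crossed-limb proportion by 1/73 = 1.4 percentage points and the standard-limb proportion by 1/202 = 0.5. These counts show scale only; the inconsistency does not depend on them.

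**The case against.** The strongest reply is that nothing is lost. The open clause can admit a death caused by the index repair. Early death has its own outcome, overall survival counts every death, and the technical success definition already covers intraoperative death and conversion. This stands. A reader might infer that index-procedure deaths are excluded from disease-specific mortality or disappear from the comparison. The text does not support that: they are not named, which is weaker.

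A second reply is that the closing words of the reintervention clause, on attribution to the aneurysm, might qualify the death and not the reintervention. An assessor's judgement would then be needed there too and the contrast would narrow, but the index EVAR would still have no 30-day rule.

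Third, the MACE row sits among short-term postoperative outcomes and speaks of a diagnosis and of 30 days, so it most naturally means a diagnosis made after surgery. A reader might infer that every patient with pre-existing cardiac failure is scored as an event. The wording does not go that far; it only fails to rule it out. A count of such patients would need both that reading and a prevalence that the document does not give.

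Fourth, all-cause death in a MACE composite can be deliberate, since it avoids judging cause of death in a trial with unblinded surgeons. This also stands. Replacing it with cardiac death would be a trade-off and not the correction of an error; cardiac cause is a different judgement from aneurysm-related cause. What remains is that the component should be labelled for what it is.

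Finally, a reader might carry the 30-day MACE wording over to long-term freedom from MACE. Table 2 defines only the 30-day version, and a condensed article may leave the other to the full protocol, so the point does not rest on that step.

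**Conclusion.** The point holds as a minor fault of definition. Aneurysm-related death has an automatic 30-day rule for aneurysm-attributable reinterventions and none for the index EVAR, so like deaths are classified alike only if an assessor uses the open clause that way. The 30-day MACE row lacks a new-or-worsened condition for cardiac failure and a coronary limit for revascularization.

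Only outcomes in the third tier are affected. The primary outcome, both secondary outcomes and the sample size are unchanged. Under the assumed 1% to 3% mortality, some 3 to 8 deaths would be open to either classification. No direction of bias can be derived from the document, and none is claimed.

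**What to change.** Reword two rows of Table 2 before outcomes are analysed.

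- **Aneurysm-related death:** add *death from any cause within 30 days of the index EVAR (including intraoperative death)* alongside the reintervention clause.
- **30-day MACEs:** change the components to *new-onset or worsened cardiac failure* and *coronary revascularization*. For death, either keep it and label it as all-cause, or report the cardiac components separately.

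No new visits or tests are needed: comorbidity is already recorded at admission and all-cause mortality is already an outcome. The costs are a slightly different event count in both outcomes, and some early deaths of unrelated cause entering aneurysm-related death, where they will overlap with 30-day all-cause mortality.

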### Data collection

Figure 1 shows the flow diagram of the trial. Once patients are admitted, baseline data will be collected for both groups, including demographic characteristics, comorbidities and anatomical variables. The demographics are collected from history taking and hospital information system. The comorbidity is evaluated by the Charlson Comorbidity Index to quantify its severity. Anatomical variables are as follows: length of aneurysm neck, oversizing ratio in proximal neck and distal limb, neck angulation, maximum diameter of aneurysm sac, intramural thrombus load of aneurysmal sac, iliac tortuosity, common iliac artery aneurysm and distal iliac calcification. We will report reasons for withdrawal for each group and compare the reasons qualitatively. Details of the procedure, consisting of operation time, radiation exposure time and contrast medium dosage, are recorded immediately after the operations. At preoperative and postoperative evaluation (24, 48, and 72 h), laboratory examinations will be conducted and corresponding results will be collected from the laboratory information system.

### Quality control

The study staff have received systematic training for recording all baseline information before initiation of the project, with a special focus on recording comorbidity and measuring parameters of AAA. Pamphlets with protocols for history taking and definitions for related comorbidity have been distributed to the staff. By computed tomography angiography, all the diameters are measured from the minor axis of axial cuts or from planes perpendicular to the centerline in reformatted slices. Two researchers will independently complete the measurement and when more than 10% differences occur, a senior member will arbitrate and give final result. Medical staffs will strictly follow the standard procedure of AAA treatment in our hospital and provide the same perioperative management or nursing care for all patients.

### Sample size calculation

We calculate the sample size for this study based on the results of our previous study (22), in which 11.5 and 7.9% of patients suffered from adverse limb events in CL and SL groups, respectively. In this trial, we hypothesize that the freedom from adverse limb events in the CL group is not inferior to that in the SL group. The predetermined non-inferiority margin on the risk difference scale (δ) is set to 0.15 between the two groups. The type I and II error rates are set to 0.05 and 0.2, respectively. As the intraoperative choice of limb configuration is difficult to randomize, the ratio of enrolled patients between the CL and SL groups is set to 4:11 based on our previous cohort study (22). After accounting for a 20% rate of dropout, it is calculated that 73 subjects are needed for the CL group, and this value is 202 in the SL group. All calculations are performed by PASS 15 software.

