**Methods:**

This is a prospective, single-center, non-randomized controlled trial. A total of 275 patients who meet the inclusion criteria will be enrolled and allocated with a 4:11 ratio of CL to SL, which is based on results of our previous study. All patients will receive same perioperative management and postoperative medications. All EVAR procedures will be performed under standard protocol, utilizing Endurant II or IIs Stent Graft. The configuration of the graft stent will be decided by surgeons and confirmed by final angiography. The primary outcome is 3-year freedom from major adverse limb-graft events (MALEs). Endpoints will be assessed at the following time points: 1, 6, 12, 24, and 36 months.

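### At the size behind 73 and 202 patients, the stated 0.05 type I error and 80% power cannot both hold for the crude risk difference: about 7% error, or about 69% power

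*Protocol article*

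**What the plan says.** All design inputs stand in the Protocol article, section Sample size calculation.

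- Event rates: "11.5 and 7.9% of patients suffered from adverse limb events in CL and SL groups, respectively".
- Margin: "The predetermined non-inferiority margin on the risk difference scale (δ) is set to 0.15 between the two groups".
- Error rates: "The type I and II error rates are set to 0.05 and 0.2, respectively".
- Allocation: "the ratio of enrolled patients between the CL and SL groups is set to 4:11 based on our previous cohort study".
- Result, after a 20% allowance for dropout: "it is calculated that 73 subjects are needed for the CL group, and this value is 202 in the SL group".
- Tool: "All calculations are performed by PASS 15 software".

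The section does not say whether alpha is one- or two-sided, which test statistic was used, or how many evaluable patients the calculation required. The section Statistical analysis plans Cox regression and a marginal structural model for time-to-event outcomes, with inverse probability weighting.

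**The concern.** A reader will take 0.05 and 0.2 as the error rates that this design delivers. The inputs make that doubtful. The CL arm is small and carries most of the variance of the difference. Its assumed risk of 11.5% doubles to 22.9% at the margin (7.9% plus 15 points), so a standard error computed at the planning rates is too small for judging the null hypothesis. Only about 7 CL events are expected (61 × 0.115 = 7.0), which is few for a normal approximation.

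In a non-inferiority trial, a type I error means accepting a CL configuration that is truly 15 points worse. If the test lets that error run above 5%, the safeguard is weaker than stated. If the test controls it, the chance of a conclusive result is lower than stated.

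**Working it through.** **1. Reproducing the plan's figure.** Unpooled normal approximation, one-sided alpha 0.05, power 80%, SL:CL ratio 11/4 = 2.75, distance to the margin 0.15 − (0.115 − 0.079) = 0.114:

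n(CL) = (1.645 + 0.842)² × (0.115 × 0.885 + 0.079 × 0.921 / 2.75) / 0.114² = 6.18 × 0.1282 / 0.0130 = 61.0

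n(SL) = 61.0 × 2.75 = 167.8, so 168. Times 1.2: 73.2 and 201.6, that is 73 and 202.

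The other variants tried do not give 73/202:

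- dividing 61/168 by 0.8: 77/210
- one-sided 0.025: about 78/213 before dropout
- pooled variance: 55/152 before dropout
- Farrington-Manning score formula: 80/221 before dropout

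**2. Standard error at the planning rates and at the boundary (61/168).**

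- Planning rates: √(0.115 × 0.885/61 + 0.079 × 0.921/168) = √(0.001668 + 0.000433) = 0.0458. CL contributes 79% of the variance.
- Boundary (22.9% v 7.9%): √(0.229 × 0.771/61 + 0.079 × 0.921/168) = √(0.002894 + 0.000433) = 0.0577, which is 26% larger.

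An unpooled Wald test estimates its standard error from the observed rates. Samples with few CL events therefore look both better and more precise, and this pushes the type I error up. A score test takes its standard error at the margin, which holds the error near its nominal level but costs power.

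**3. Exact size and power.** Both binomials were enumerated in full, at nominal one-sided 0.05. Size is at 22.9% v 7.9%; power is at 11.5% v 7.9%.

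| Evaluable CL/SL | Wald size | Wald power | Score size | Score power |
|---|---|---|---|---|
| 61/168 | 7.0% | 77.6% | 4.6% | 69.5% |
| 58/162 (73/202 less 20%) | 7.0% | 75.7% | 4.7% | 67.3% |
| 73/202 (no dropout) | 6.8% | 83.1% | 4.7% | 76.9% |

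A 400,000-run simulation of the Wald test at 61/168 gave 7.0% and 77.6%.

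**4. Does the shortfall depend on choosing the score test?** No. A most-powerful-test bound over null points on the margin gives at most about 71.5% power at 61/168 for any test whose true size is no more than 5%. At 73/202, with nobody lost, the bound is 78.3%. The score test reaches 80% power at about 80/220 evaluable (exact 80.8%).

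**5. If alpha is meant as one-sided 0.025 (61/168).** Wald: size 4.1%, power 68.5%. Score: size 2.2%, power 55.6%.

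**The case against.** The strongest reply is that nothing was miscalculated. The error rates are nominal inputs, a standard large-sample formula turns them into 73/202, and under that formula power at 61/168 is 80.0%. That stands: a reader might infer an arithmetic error, and the document does not support it. It does not rescue the stated properties, because no test of true size 5% reaches 80% power at that size.

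Second, the test, the sidedness and 61/168 are inferred, and the choice of test may be settled in a fuller plan that is not shown. That also stands. A reader might infer that the trial will accept a configuration 15 points worse 7 times in 100. That follows only if an unpooled interval is used at one-sided 0.05. With a two-sided 95% interval the unpooled size is 4.1%, within 0.05, and what remains is a larger loss of power.

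Third, the planned analysis is weighted Cox regression and a marginal structural model, not a crude comparison of two proportions. A reader might take 69.5% as the trial's actual power; the document does not support that either. The margin and the sample size were, however, set on the risk-difference scale, so the crude comparison is the right benchmark for the sample-size statement.

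Fourth, the pair 7% and 69% comes from two different tests. The reconstructed method's own exact power is 77.6%, only 2.4 points short of 80%, but it has that power at 7% error.

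**Conclusion.** The point holds as a sample-size and power statement that the design does not deliver. For the crude 3-year risk difference at 61/168, the stated rates cannot both be true: either the type I error is about 7.0% with 77.6% power, or it is held at about 4.6% with 69.5% power. At 58/162 the power figures are 75.7% and 67.3%.

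This rests on the planning rates of 11.5% and 7.9%, a one-sided alpha of 0.05, and a reconstruction of 61/168 that fits the printed numbers but is not printed itself. It also rests on every evaluable patient having a known 3-year outcome. The score test's size is close to nominal rather than guaranteed: it reached 5.4% at the worst null point examined. The effect of weighting and censoring is not quantified here.

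**What to change.** Keep the enrolment of 275. In Sample size calculation:

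- State whether alpha is one- or two-sided, and name the test behind the calculation.
- Restate power as about 69% at 61/168 and about 67% at 58/162 evaluable. Label it a planning figure for an unadjusted comparison at one-sided 0.05, before any loss from weighting or censoring.

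In Statistical analysis, say that the 0.15 margin is tested with a risk-difference method that holds its size. For the crude difference, a Farrington-Manning or Miettinen-Nurminen interval would serve. For the weighted difference, use an interval other than unpooled Wald, chosen by the trial statistician.

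The cost is wording and a less favourable stated power. The fix makes the statement true; it does not bring power up to 80%. With the score test that would take about 80/220 evaluable, or 100/275 enrolled at 20% loss (80/0.8 and 220/0.8).

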### Statistical analysis

Categorical data is expressed as number and rate, while continuous data is expressed as means ± standard deviation if they are normally distributed or median with interquartile range otherwise. Student’s *t*-test or Mann-Whitney *U*-test is used for univariate analysis of continuous data. χ^2^-test or Fisher’s exact test is used for categorical data. For primary analyses, multivariate logistic regression is used to calculate adjusted odds ratio and 95% confidence interval for short-term outcomes. Cox proportional hazard regression analysis and marginal structural model are adopted to assess the association between limb configuration and time-to-event outcomes.

The propensity score to undergo CL or SL is estimated by logistic regression model based on demographic and anatomic information. Inverse probability of treatment weighting adjusted analyses are performed to achieve weighted balance with standardized differences < 0.10. Sensitivity analysis is conducted to stabilize the weights by truncating the non-overlapping tails of the propensity score distributions which below or above the 1st and 99th percentiles. Subgroup analysis is conducted in terms of large aneurysm sac, severely angulated neck, tortuous iliac arteries and iliac landing zone (whether using bell-bottom iliac stent graft). In addition, this analysis will be carried out in AP and LR subgroups. R studio Version 1.2.1335^1^ and Empower (X&Y solutions, Inc., Boston, MA)^2^ are utilized for statistical analysis.

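### The 73 + 202 enrolment target does not give 80% power after 20% dropout: the allowance appears to be ×1.2 rather than ÷0.8, and the target fits only a one-sided 5% test that the protocol does not state

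*Protocol article*

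**What the plan says.** All the inputs are in the protocol article under Sample size calculation.

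- Event rates come from the centre's previous cohort, "in which 11.5 and 7.9% of patients suffered from adverse limb events in CL and SL groups, respectively".
- The aim is non-inferiority: "we hypothesize that the freedom from adverse limb events in the CL group is not inferior to that in the SL group".
- Margin: "The predetermined non-inferiority margin on the risk difference scale (δ) is set to 0.15 between the two groups".
- Error rates: "The type I and II error rates are set to 0.05 and 0.2, respectively". Whether the type I error is one- or two-sided is not said.
- Allocation: "the ratio of enrolled patients between the CL and SL groups is set to 4:11 based on our previous cohort study".
- Result for the crossed-limb arm: "After accounting for a 20% rate of dropout, it is calculated that 73 subjects are needed for the CL group".
- Result for the standard-limb arm: 202 patients. The abstract repeats the total of 275.

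The section prints neither the numbers before dropout nor the way the allowance was applied. Under Statistical analysis, the one interval level given is in "adjusted odds ratio and 95% confidence interval", and that sentence concerns short-term outcomes. For time-to-event outcomes the article names Cox regression and a marginal structural model, with no interval level.

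**The concern.** If a fraction d of patients is lost, N/(1−d) must be enrolled to keep N. Multiplying by (1+d) gives too few. With d = 0.20 the two factors are 1.25 and 1.20, and the stated targets look like the second. If so, at the dropout rate the protocol itself assumes, the trial ends with fewer evaluable patients than its own calculation requires, and the 80% power statement is not met.

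The unstated sidedness makes this harder to see. A reader who takes 0.05 as two-sided cannot reproduce the target, and the power depends noticeably on which reading governs the non-inferiority decision.

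**Working it through.** **Inputs** (all from Sample size calculation): freedom from events 0.885 (CL) and 0.921 (SL); expected difference 0.115 − 0.079 = 0.036 against CL; margin 0.15, so the distance to the margin is 0.15 − 0.036 = 0.114; power 0.80; SL:CL = 11/4 = 2.75; dropout 20%. One-sided 0.05 is my reading of alpha, tested below.

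**Step 1: evaluable patients, unpooled Z test.**

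n_CL = (z_α + z_β)² × [p_C(1−p_C) + p_S(1−p_S)/2.75] / 0.114²

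- (1.645 + 0.842)² ≈ 6.183
- 0.115×0.885 + 0.079×0.921/2.75 = 0.10178 + 0.02646 = 0.12823
- n_CL = 6.183 × 0.12823 / 0.012996 ≈ 61.0
- n_SL = 2.75 × 61.0 ≈ 167.8

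This gives 61 and 168, with power 80.0%.

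**Step 2: dropout allowance.**

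| Allowance | CL | SL | Total |
|---|---|---|---|
| ×1.2 | 73.2 | 201.6 | 73 + 202 = 275 (as stated) |
| ÷0.8 | 76.25 → 77 | 210 | 287 |

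The loss that ×1.2 covers is 1 − 1/1.2 = 16.7%.

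**Step 3: do other standard methods explain 73/202?** Figures are CL/SL.

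| Method | Before dropout | After ÷0.8 |
|---|---|---|
| Unpooled, one-sided 0.025 | 78/213 | 97/267 |
| Pooled, one-sided 0.05 | 56/152 | about 70/190 |
| Continuity-corrected unpooled, one-sided 0.05 | 73/200 | 91/249 |
| Farrington-Manning, one-sided 0.05 | 81/223 | 101/278 |

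None gives 73/202 with the correct inflation. The continuity-corrected size comes close before dropout (73/200), but it misses the SL figure and would mean that no dropout allowance was made, contrary to the text. At one-sided 0.025, the size before any dropout already exceeds the target.

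**Step 4: power at the stated enrolment and dropout.** 73 × 0.8 = 58.4 and 202 × 0.8 = 161.6, so about 58/162.

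- SE = √(0.10178/58 + 0.07276/162) = 0.04695
- 0.114/0.04695 = 2.428
- One-sided 0.05: Φ(2.428 − 1.645) = Φ(0.783) = 78.3%
- One-sided 0.025 (two-sided 95% interval): Φ(2.428 − 1.960) = Φ(0.468) = 68.0%

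Exact enumeration of the same Wald test at one-sided 0.05 gives 77.6% at 61/168 and 75.7% at 58/162. The absolute level is a little lower, but the loss from the dropout step is again about 2 points.

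**The case against.** **The effect is small, and 20% loss may not occur.** The dropout step costs 287 − 275 = 12 patients (4.4% of 275) and 1.7 power points. With no loss, 73/202 would have 85.9% power. The Follow-up section provides for telephone or WeChat contact and for records from local hospitals, and patients censored in a Cox model still contribute time. All this stands and limits the severity. It does not make the sentence right, because the article says that 20% has been allowed for.

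**The ×1.2 step is inferred.** That is true. It rests on a match in both arms after rounding (168 before inflation, then 73.2 to 73 and 201.6 to 202). Only the software output could confirm it.

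**Unstated sidedness is an omission, not an error.** This largely stands. A non-inferiority test is one-sided by construction, one-sided 0.05 is a permissible reading, and on that reading the section is consistent about alpha. The decision interval may also be left to an analysis plan. Sidedness is raised here only because the corrected power statement cannot be written without it.

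**A stronger reading to avoid.** A reader might infer from "adjusted odds ratio and 95% confidence interval" that non-inferiority will be judged on a 95% interval and that true power is therefore about 68%. The article does not support this. That interval belongs to odds ratios for short-term outcomes, whereas the primary outcome is 3-year freedom from MALEs, for which no level is given.

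**The recomputed power is for a simple comparison of proportions.** This also stands. The planned analysis uses propensity weighting, Cox regression and a marginal structural model, so 78% describes the article's own sample size model and does not predict the power of the weighted analysis.

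**Conclusion.** The statement that 73 + 202 gives 80% power after 20% dropout is wrong as written. At one-sided 5%, the stated inputs need 61/168 evaluable. The target leaves about 58/162 at 20% loss, which gives about 78% power, and it reaches 80% only up to about 16.7% loss. Enrolment of 77 + 210 = 287 would be needed to support the claim.

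This rests on the stated event rates, margin and ratio, an unpooled Z test at one-sided 0.05, and an unadjusted two-proportion comparison. The 68% figure is conditional on a two-sided 95% decision rule that the article does not state. Severity is minor to moderate: the figure should be corrected, but a shortfall of about 2 points does not threaten the trial.

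**What to change.** Keep 275 patients and correct the wording under Sample size calculation:

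1. Check against the software output, then state that the type I error is one-sided 0.05, corresponding to a two-sided 90% interval for the non-inferiority decision.
2. Give the evaluable numbers before dropout (61 and 168).
3. Either state that 275 enrolled with 20% dropout leaves about 58 CL and 162 SL and about 78% power for the unadjusted two-proportion comparison, or state that the allowance covers about 16.7% dropout at 80% power.

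This costs wording only and a slightly less favourable power statement. If 80% power after 20% loss is to be claimed, the target becomes 287, which is 12 more patients.

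If a two-sided 95% interval is to decide, say so and restate power as about 68%. Reaching 80% on that rule would need 97 + 267 = 364 enrolled, which is 89 more.
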